## Outcomes

### Primary outcome

#### Exacerbation rate

Primary outcome is exacerbation rate. An exacerbation is defined as sustained worsening of respiratory symptoms during 48 h requiring oral corticosteroid, antibiotic or combination treatment that was initiated by a physician. Respiratory symptoms include at least one of the Anthonisen criteria, which are increased dyspnoea, sputum volume or sputum purulence, with or without minor symptoms such as cough, fever, common cold, wheezing or sore throat [38]. Participants will register symptoms and changes in medication on a diary card during the whole study period. During each telephone contact and study visit diary cards will be discussed and reviewed. Also questions will be asked regarding hospitalization during the last months. If necessary, information on changes in medication and COPD exacerbations during the study period will be confirmed through contact with the providing pharmacist, the general practitioner and hospital.

### Secondary outcomes

#### Time to first and second exacerbation and time to fist hospitalisation

Time to first and second exacerbation and time to first hospitalisation will be registered on the basis of the diary card and interviews.

#### Use of antibiotic and corticosteroids

With the use of earlier mentioned diary card and interviews the use of antibiotics and corticosteroids will be registered.

#### Spirometry measures

At t = 0 and t = 12 participants will undergo spirometry. The spirometry will be performed according to American Thoracic Society/European Respiratory Society (ATS/ERS) guidelines [39]. Only post-bronchodilator forced expiratory volume in one second (FEV_1_) and forced vital capacity (FVC) will be determined. Measurements will take place after inhalation of the sympathomimetic salbutamol and/or the anticholinergic ipratropium bromide. Inspiratory capacity (IC) and expiratory reserve volume (ERV) will also be determined according to ATS/ERS guidelines [39].

#### Lung volumes

Measurements of absolute lung volume, residual volume (RV), functional residual capacity (FRC) and total lung capacity (TLC) will be assessed by body plethysmography according to guidelines of the ATS/ERS task force at t = 0 and t = 12 [40, 41].

#### Maximal respiratory mouth pressures

Respiratory muscle strength will be tested by measurement of the maximal inspiratory and expiratory mouth pressure (MIP and MEP, respectively). Measurement will be made with a mechanical pressure gauge that is connected to a mouthpiece according to the revised ATS guideline [42].

#### Physical performance

During every visit (t = 0, t = 6 and t = 12), participants will perform physical performance tests.

In the 6-min walking test the participant is asked to walk as far as possible during a period of 6 min. The participant will walk up and down a hallway. The 6-min walking test is performed according to the ATS guidelines [43].

In the chair-stands-test the participant will be asked to fold his arms across his chest and to stand up from a sitting position and sit down five times as quickly as possible [44, 45].

In the 3-meter walking test the participant is asked to walk three meters, turn around 180° and walk back [44, 46].

In the tandem test the participant is asked to stand with the heel of one foot directly in front of, and touching the toes of, the other foot for at least 20 s with his eyes open and closed [44, 47].

#### Muscle strength

Muscle strength will be assessed with measurement of hand grip strength. The participant is seated in a chair and holds the dynamometer in the hand, with the arm at right angles and the elbow by the side of the body. The handle of the dynamometer is adjusted if required. When ready, he squeezes the dynamometer with maximum isometric effort, which is maintained for about 5 s. No other body movement is allowed. This measurement will be performed three times with both hands [48].

#### Quality of life

Quality of life will be assessed by three questionnaires These will be completed at every study visit.

The St. George’s Respiratory Questionnaire (SGRQ) is designed to measure health impairment in patients with asthma and COPD [49, 50] and produces a symptoms score and an activity and impacts score.

The Short Form 12 health Survey (SF-12) is a multipurpose short-form generic measure of health status [51]. It is a validated subset of the larger SF-36 and monitors health in general and in specific populations. These scores correlate highly with the SF-36 versions [52]. The SF-12 has been previously used in patients with COPD [50, 53].

The Clinical COPD questionnaire (CCQ) is a simple 10-item, health-related quality of life questionnaire with good psychometric properties [54]. The questionnaire is responsive to pulmonary rehabilitation and a minimal clinically important difference has recently been defined [55].

#### Anxiety and depression

Anxiety and depression will be assessed by means of two questionnaires and will be completed at every study visit. The Hospital Anxiety Depression Scale (HADS) is a questionnaire measuring feelings of depression and anxiety [56]. Reliability and validation of the Dutch translation of the HADS has been reported [57]. The HADS is frequently applied in research in patients with COPD [58, 59].

The Center for Epidemiologic Studies Depression Scale (CES-D) is a self-report scale designed to measure depressive symptoms in the general population. The development of the scale has been described in detail elsewhere [60]. The scale has been used in several COPD populations [61, 62].

#### Physical activity

Physical activity will be assessed by the Short QUestionnaire to ASses Health enhancing physical activity (SQUASH). SQUASH is a self-report instrument to measure habitual physical activity [63]. The questionnaire has been used in COPD populations [64].

#### Antimicrobial peptides and pro-inflammatory mediators in nasal secretions

Nasal secretions will be collected by vacuum-aided suction to prevent dilution that occurs when using lavage-based methods [65]. The nasal secretions will be analysed for the presence of antimicrobial peptides and pro-inflammatory cytokines (hCAP18/LL-37, HNP1-3, NGAL, IL-1ß, TNF-α, IL-6) using enzyme-linked immunosorbent assays (ELISA).

#### Typing of bacteria and viruses in nasal secretions

A nasal swab will be obtained using standard procedures. PCR on presence of bacteria and respiratory viruses (non-typeable *Haemophilus influenzae*, *Streptococcus pneumoniae*, *Moraxella catarrhalis* and a panel of respiratory viruses including rhinovirus) will be performed.

#### Inflammation and host response against infectious agents

In one of the academic centers peripheral blood mononuclear cells (PBMC) and platelets will be derived from 50 participants before and after the intervention. Venous blood will be drawn in EDTA and 3.2 % sodium citrate tubes after which PBMC and platelet-rich plasma (PRP) will be isolated, washed and suspended. PBMC will be stimulated with various agonists to TLR (bacterial, fungal and viral) and with microbial stimuli. The following stimuli will be used: RPMI (control), LPS (TLR4), Pam3Cys (TLR2), Poly (I:C) (TLR 3), *Streptococcus pneumoniae, Non-typeable Haemophilus influenza, Pseudomonas aeroginosa, Aspergillus fumigatus*, sonicated *Mycobacterium avium* and *Candida albicans*. Pro- and anti-inflammatory cytokines will be measured before and after stimulation: TNF-α, Il-1ß, IL-6, IFN-γ (24 h incubation) and IL-10, IL-17 and IL-22 (7 days incubation). All cytokines will be measured in cell culture supernatants using ELISA. PRP will be used for analyses of platelet function in terms of activation and aggregation. Second, phenotyping of circulating immune cells will be done using advanced multiparameter flowcytometry and functional readouts. A whole blood staining will be used to be able to calculate absolute numbers of CD4 (including Treg), CD8 T cells, NK cells, B cells and monocytes. Next, a detailed phenotypic analysis of the T cell compartment will be performed by additional staining of whole blood or isolated PBMC using antibodies. Functional characteristics of the T cell compartment (CD4+, CD8+, CD4+/Foxp3+ (Treg)) with respect to cytokine production (IFN-γ, IL-2, IL-4, IL-5, IL-10 and IL-17A) and their associated transcription factors (Tbet, Gata-3, RORyt) will be analysed.

### Sample size calculation

The study is designed to demonstrate a minimum difference of one exacerbation per patient-year between the vitamin D and the placebo group. We based our assumptions on post-hoc analyses of the RCT by Lehouck et al.[30], which had a similar patient sample, although without selection for vitamin D deficiency. Based on differences in Poisson means, a sample size of 94 participants per group is needed to demonstrate a difference of 1 exacerbation per patient-year with 80 % power at 5 % significance. This number was based on the assumption of 2.45 exacerbations per patient-year in the intervention group and 3.45 in the placebo group. To account for a dropout rate of 20 % 120 participants will be recruited per study group.

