**Methods/Design:**

We will perform a randomised, multi-center, double-blind, placebo-controlled intervention study. The study population consists of 240 COPD patients aged 40 years and older with vitamin D deficiency (25-hydroxyvitamin D concentration < 50 nmol/L). Participants will be recruited after an exacerbation and will be randomly allocated in a 1:1 ratio to receive vitamin D3 16800 IU or placebo orally once a week during 1 year. Participants will receive a diary card to register the incidence of exacerbations and changes in medication during the study period. Visits will be performed at baseline, at 6 months and at 12 months after randomisation. Participants will undergo spirometry, measurement of total lung capacity and assessment of maximal respiratory mouth pressure. Several physical performance and hand grip strength tests will be performed, questionnaires on quality of life and physical activity will be filled in, a nasal secretion sample and swab will be obtained and blood samples will be taken. The primary outcome will be exacerbation rate.

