## Methods

### Study design and participants

The study is designed as a randomised double-blind, multi-center, placebo-controlled trial, with an intervention (*n* = 120) and a control group (*n* = 120). The study population consists of COPD patients with GOLD stages II-IV. Participants will be included if they have a vitamin D deficiency (25(OH)D concentrations <50 nmol/L) and a recent exacerbation of COPD. The eligibility criteria are described in Table 1. Participants will be recruited if they present with an exacerbation of COPD at the outpatient clinic or emergency ward. Screening serum 25(OH)D concentration will be measured during the exacerbation period. Inclusion and randomisation will take place 6–8 weeks after recruitment or at a later time point as soon as the participant has recovered. An exacerbation is defined as sustained worsening of respiratory symptoms during 48 h requiring oral corticosteroid, antibiotic or combination treatment that was initiated by a physician [38]. Convalescence is defined as recovery to the stable state. The recruitment will start in three academic hospitals and five peripheral hospitals in the surroundings of the academic centers. Study visits will be performed at baseline (t = 0), 6 months (t = 6) and 12 months (t = 12) after randomisation as depicted in Fig. 1. Participants will be contacted by telephone at 2, 4, 8 and 10 months The study is approved by the Medical Ethics Committee of the VU University Medical Center, Radboud University Medical Center and Leiden University Medical Center. Written informed consent will be obtained from all participants.

**Table 1 Tab1:** Eligibility criteria for the PRECOVID trial

Inclusion criteria	Exclusion criteria
Vitamin D deficiency (serum 25(OH)D < 50 nmol/l)	Severe vitamin D deficiency (serum 25(OH)D <15 nmol/l),
Postbronchodilator FEV_1_/FVC < 0.70, FEV_1_ < 80 % and diagnosis COPD confirmed by a physician	Use of a supplement containing more than 400 IU vitamin D per day
Recent COPD exacerbation	Use of maintenance dose oral corticosteroids
≥10 packyears of smoking	Diagnosed asthma
Age ≥ 40 years	Diagnosed osteoporosis
Written informed consent	Self-reported history of hypercalcaemia or nephrolithiasis
Ability to comply with all study requirements.	Self-reported presence of sarcoidosis
	Diagnosed chronic kidney disease stage 4 or higher (eGFR ≤ 29 ml/min/1.73 m2)
	Interfering malignant diseases
	Life expectation of less than 1 year on the basis of concurrent disease

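### The stated 94 participants per group does not follow from its inputs: Poisson means of 2.45 and 3.45 need about 47 per group, so 94 implies an undeclared factor of about two

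*Protocol article*

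**What the plan says.** The Sample size calculation section gives a complete set of inputs. The target is a difference of one exacerbation per patient-year, and the assumed rates are "2.45 exacerbations per patient-year in the intervention group and 3.45 in the placebo group". The method and result are given as "Based on differences in Poisson means, a sample size of 94 participants per group is needed to demonstrate a difference of 1 exacerbation" per patient-year, and the operating characteristics as "with 80 % power at 5 % significance". The number is then raised to 120 per group for 20% dropout, and the Study design and participants section repeats 120 per arm.

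Three further facts matter. The abstract says that participants "will be randomly allocated in a 1:1 ratio". The Intervention section fixes treatment at 12 months, so each completer contributes one patient-year. The primary analysis is a Poisson generalised linear model reporting a rate ratio with a 95% confidence interval. No standard deviation, dispersion parameter or variance inflation appears anywhere in the article.

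**The concern.** A Poisson distribution sets the variance equal to the mean. Once the two rates, the follow-up time, alpha and power are given, the sample size is therefore determined up to the choice of approximation. Those approximations differ by a few participants, not by a factor of two. Yet 94 is exactly twice 47, the per-group number that the usual formulas return.

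This number justifies recruiting 240 patients. If 94 was a total, the trial is about twice the size that its stated assumptions require, and no allowance for overdispersion was planned. If an overdispersion factor was built in, the size may be reasonable, but the article then sizes the trial under one variance assumption and names an analysis model under another. A reader cannot tell which applies.

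**Working it through.** **Inputs.** Rates λ₁ = 2.45 and λ₂ = 3.45, power 80%, alpha 5% (Sample size calculation); allocation 1:1 (abstract); one year per participant (Intervention). Sidedness is not stated. Two-sided is taken as the main case because it matches the planned 95% confidence interval. Then (1.960 + 0.842)² = 7.849.

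**Attempt to reproduce 94 per group** (two-sided, 80% power, n per group):

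- Difference in means: 7.849 × (2.45 + 3.45) / 1² = 46.3, so 47.
- Log rate ratio: 7.849 × (1/2.45 + 1/3.45) / [ln(3.45/2.45)]² = 7.849 × 0.698 / 0.1172 = 46.8, so 47.
- Log rate ratio with pooled null variance: 45.8, so 46.
- Square-root transform: 7.849 / [2 × (√3.45 − √2.45)²] = 46.0, so 46.
- Exact conditional test: 48 (power 80.0%; 47 gives 79.2%).
- Both variances set to the larger rate: 7.849 × 2 × 3.45 = 54.2, so 55.

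A one-sided 5% test gives 37 on the difference scale, further from 94. At 90% power the two-sided number is 62 to 63, and at 95% power 77 to 78. None of these reaches 94 per group at the stated 80%. Two groups of 47 make 94 in total.

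**Dropout step.** 94 / 0.8 = 117.5, so 118, rounded up to 120. This step is sound. From 47, the same step gives 58.75, so 59 per group or 118 in total.

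**Power at the stated size, under the stated Poisson rates.**

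- 94 per group: 97.9% on the difference scale, 97.8% on the log scale, 97.7% exact.
- 120 per group: 99.5% on the difference scale, 99.4% exact.

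**What would make 94 per group correct at 80% power.**

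- A variance-to-mean ratio of 94 / 46.3 = 2.03 (difference scale) or 94 / 46.8 = 2.01 (log scale).
- Negative binomial dispersion k solving 94 = 7.849 × (0.698 + 2k) / 0.1172, which gives k = 0.35 (0.34 on the difference scale).
- About half a year of exposure: 46.3 / 0.5 = 92.6, so 93. This would contradict the one-year design.

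With a variance-to-mean ratio of 2, power is 80.6% at 94 per group and 51% at 47 per group.

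**Consequence for the planned model.** If the variance is twice the mean, plain Poisson standard errors are too small by √2. The nominal critical value of 1.96 then acts as 1.96/√2 = 1.386, and the two-sided type I error is about 17%.

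**Sensitivity to dispersion.** The article gives no dispersion, so this range of k is an assumption for illustration. With 94/0.8 rounded to 120 and 20% lost, 120 × 0.8 = 96 completers per group. On the log scale, power is about 89% (k = 0.2), 81% (k = 0.35), 73% (k = 0.5) and 64% (k = 0.7).

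**The case against.** The strongest reply is that 94 per group may be right and only the reporting incomplete. A variance factor of 2 on the log scale gives 2 × 46.8 = 93.5, so 94, which fits as well as a mislabelled total. The assumptions come from post-hoc analyses of an earlier trial, and the article condenses a fuller protocol, so an overdispersion allowance could have been made there. This stands as a possible explanation and rules out any claim to know which error occurred. It does not rescue the text: the article names a Poisson calculation, and a Poisson calculation on these rates does not give 94.

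Three stronger readings may tempt a reader, and the document supports none of them.

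- The trial is underpowered, or should be cut to 47 per group. On its stated assumptions it has more power than claimed, and if overdispersion was assumed, 47 per group would have only 51%.
- A null result could not be interpreted. The rate ratio will be reported with its 95% confidence interval, and a null result is read from that interval rather than from design power.
- Power of 80% is fragile because it holds at a single dispersion value. At 96 per group it is at least 80% for every k up to about 0.37, and at 120 with full exposure up to about 0.55. The intention-to-treat set can also include partial follow-up from dropouts, so 96 is a conservative basis.

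**Conclusion.** The point holds as a sample size that cannot be reproduced and is wrong on its own stated inputs. Those inputs give about 46 to 48 per group two-sided (55 with both variances at the higher rate, 37 one-sided), against a stated 94. Power at 94 per group under the stated rates is about 98%, not 80%. The factor of two lies in the sample size or in the variance behind it. The stated 80% would be right if an undeclared variance-to-mean ratio of about 2 had been used.

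This rests on one full year of exposure per participant, 1:1 allocation and a two-sided test; a one-sided test widens the gap. Whether a total was labelled as per group or an allowance was left unreported cannot be settled from the article.

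**What to change.** Keep 120 per group, state the sidedness of the test, and restate the calculation in one of two ways:

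- If plain Poisson was intended, say that about 47 per group would suffice for 80% power and that 94 evaluable per group gives about 98%.
- If overdispersion was allowed for, declare the variance inflation (about 2, or k about 0.35) that leads to 94 per group at 80% power, and give its source.

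In the second case, add a matching dispersion term to the primary analysis in the Statistical analysis section: quasi-Poisson or robust variance, or a negative binomial model. The article currently names only a Poisson model, so this would be a change to the plan. Any table of power over a range of k should be labelled as an assumption.

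The cost is a few sentences in the sample size section and, in the second case, one line in the model specification. Enrolment does not change.

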### Statistical analysis

#### Primary outcome

The primary outcome of the trial, exacerbation rate, will be analysed with generalized linear models for a Poisson distribution. Analyses will be adjusted for the variables included in the balancing algorithm for randomisation, i.e. study center, gender, age and current smoking. The outcomes will be presented as rate ratios with their 95 % confidence interval.

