## Introduction

Chronic obstructive pulmonary disease (COPD) is characterized by a persistent airflow limitation and an abnormal inflammatory response of the airways. COPD is predicted to be the third worldwide cause of mortality by 2020 [1]. Exacerbations in COPD determine disease-associated morbidity and mortality [2]. Patients with frequent exacerbations have a more rapid decline in lung function, worse quality of life and decreased exercise performance. Yet, effective treatment alternatives to prevent exacerbations are still lacking.

Vitamin D deficiency is highly prevalent in patients with COPD [3, 4]. Traditionally, vitamin D is associated with bone health. The discovery of the presence of vitamin D receptors (VDR) in many other cells, such as monocytes, macrophages, muscle cells and endothelial cells, has elicited hypotheses of direct vitamin D effects on these cells. These hypotheses are further strengthened by local 25-hydroxyvitamin D-1-alpha-hydroxylase activity, which converts the inactive 25-hydroxyvitamin D (25(OH)D) to the active 1,25-dihydroxyvitamin D (1,25(OH)_2_D), in many of these cells. The presence of vitamin D receptors on immune cells [5] and the high prevalence of vitamin D deficiency among COPD patients has given rise to the hypothesis that vitamin D might have a potential effect in preventing exacerbations in patients with COPD [6].

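### The primary Poisson model makes no allowance for overdispersion; if patients differ in exacerbation proneness beyond four covariates, its standard error is too small and its 95% interval too narrow

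*Protocol article*

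**What the plan says.** Under Statistical analysis, Primary outcome, the protocol article states: "The primary outcome of the trial, exacerbation rate, will be analysed with generalized linear models for a Poisson distribution". It continues: "Analyses will be adjusted for the variables included in the balancing algorithm for randomisation, i.e. study center, gender, age and current smoking", and "The outcomes will be presented as rate ratios with their 95 % confidence interval". Neither that section nor Secondary outcomes below it names a dispersion parameter, scale factor, robust variance, negative binomial alternative or check for overdispersion. The covariates include neither exacerbation history nor disease severity.

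The Sample size calculation also rests on Poisson means, with "2.45 exacerbations per patient-year in the intervention group and 3.45 in the placebo group", and states no dispersion term.

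On variation between patients, the Introduction remarks: "Patients with frequent exacerbations have a more rapid decline in lung function, worse quality of life and decreased exercise performance". Study design and participants admits GOLD stages II to IV from academic and peripheral hospitals.

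**The concern.** A Poisson model for exacerbation counts treats all patients with the same centre, gender, age and smoking status as having one underlying rate. If some are more prone to exacerbations than others for reasons outside those four variables, the counts vary more than the model allows. Its standard error is then too small, the 95% interval covers less than 95%, and the test rejects a true null hypothesis more than 5% of the time.

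This affects the trial's primary comparison, in the direction that favours a false claim of effect. Randomisation protects the rate ratio estimate, so the fault would lie in the standard error, interval and p-value alone.

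**Working it through.** **The plan's own figure.** With 2.45 and 3.45 exacerbations per patient-year, 80% power and two-sided 5% (sidedness is not stated and is assumed here), and one year per patient:

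- Difference of Poisson means: n = (1.96 + 0.842)² × (2.45 + 3.45) / 1² = 7.849 × 5.90 = 46.3 per group.
- Log rate ratio: n = 7.849 × (1/2.45 + 1/3.45) / [ln(2.45/3.45)]² = 7.849 × 0.698 / 0.1172 = 46.8 per group.

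The stated 94 per group is therefore not reproduced. The dropout step is consistent: 94 / 0.8 = 117.5, close to the 120 planned. The gap between 94 and 46–47 is a separate sample-size matter, and nothing below depends on it.

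**Effect of overdispersion on the primary test.** Inputs:

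- Rate of 3.45 per year in both arms (the stated placebo rate, under the null hypothesis).
- 120 per arm and 20% dropout, from the Sample size calculation.
- Gamma-distributed patient rates with dispersion k. The document gives no k, so 0 to 0.5 is an assumption. It should be read as the dispersion left after the four covariates, because the calculations are unadjusted.

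Formulas:

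- Variance/mean: φ = 1 + 3.45k
- Type I error: 2 × [1 − Φ(1.96/√φ)]; coverage is 1 minus this
- Interval width relative to the correct width, log scale: 1/√φ

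Example, k = 0.2: φ = 1.69, √φ = 1.30, 1.96/1.30 = 1.51, so type I error is 13.2%.

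| k (assumed) | φ | Type I, formula | Type I, simulated, full year | Type I, simulated, 20% dropout | Coverage, formula | Relative width |
|---|---|---|---|---|---|---|
| 0 | 1.00 | 5.0% | 5.1% | 4.9% | 95% | 1.00 |
| 0.1 | 1.35 | 9.1% | 9.2% | 9.0% | 91% | 0.86 |
| 0.2 | 1.69 | 13.2% | 13.0% | 12.6% | 87% | 0.77 |
| 0.35 | 2.21 | 18.7% | 18.4% (k = 0.34) | 18.0% | 81% | 0.67 |
| 0.5 | 2.73 | 23.5% | 23.3% | 23.1% | 76% | 0.61 |

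The full-year column is from 40,000 simulated null trials with 120 per arm. The dropout column is from 20,000, with dropout at uniform times and person-time as denominator. A further simulation with dropout agreed within 0.4 percentage points for k from 0.1 to 0.5.

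**Does a changed variance cure it?** In the full-year simulations over k = 0 to 0.5, a robust (sandwich) standard error gave about 5.3% and a Pearson-scaled one 5.1–5.2%. With dropout, the robust standard error gave 5.2–5.4%.

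**Power under a valid analysis.** For 120 × 0.8 = 96 completers per arm and the planned rates, power = Φ(|ln(2.45/3.45)| / √[(1/2.45 + 1/3.45 + 2k)/96] − 1.96). This gives 98% at k = 0, 94% at 0.1, 89% at 0.2, 81% at 0.35 and 73% at 0.5.

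**The case against.** The strongest reply is that the article names a distribution family, not a variance estimator. A scaled or sandwich standard error would fit the same sentence and may be in a fuller plan not shown. That is fair, and it limits the point: the fault arises if the stated model is followed as written, with its default variance. A pre-specified correction elsewhere would answer it.

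It is also fair that the evidence for heterogeneity within the document is modest. The Introduction's remark concerns prognosis, and some patients having more events than others is expected under a pure Poisson process. Every participant needs a recent exacerbation, and several groups are excluded, which narrows the population. The four covariates would absorb whatever heterogeneity they explain. Overdispersion is plausible here, not shown, so every error rate above is conditional on k.

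Two stronger readings are tempting, and the document supports neither:

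- A reader might infer that the planners expected a variance twice the mean, because 94 is about twice 47, and that the analysis discards it. But the text says only: "Based on differences in Poisson means, a sample size of 94 participants per group is needed". A total of 94 read as a per-group number explains the figure equally well. A larger sample would in any case protect power, not type I error.
- A reader might infer that follow-up time is ignored because no offset is mentioned. But the outcome is a rate, it is reported as rate ratios, and the design works per patient-year. Leaving out the word offset is ordinary for an article.

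**Conclusion.** The point holds in conditional form. The stated primary model is Poisson, has no stated allowance for overdispersion, and adjusts for nothing that measures exacerbation history or severity. If heterogeneity remains after the four covariates, nominal 5% becomes 9% at k = 0.1 and about 23% at k = 0.5; with none it stays at 5%. These figures assume gamma-distributed rates, 3.45 events per year in both arms and model-based standard errors. They are not an estimate of this trial's actual error rate, because no dispersion value is given. The rate ratio estimate is not in question.

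**What to change.** Replace the model sentence with one that pre-specifies, before unblinding, an analysis robust to overdispersion. Either negative binomial regression, or Poisson regression with a robust (sandwich) or Pearson-scaled variance, is sufficient; negative binomial is not required. Keep the same four covariates and name follow-up time as the denominator. Plain Poisson can remain as a sensitivity analysis at most.

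The cost is one sentence, and a wider interval if overdispersion is present, with the power shown above. If it is absent, little is lost. Fixing the choice now also avoids a change of model prompted by the data.

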### Randomisation and masking

For treatment allocation in this trial, we will apply the sequential balancing method with study center as the first step in the balancing algorithm, followed by gender, age and current smoking. These variables are (potential) prognostic factors and thus should be balanced over the treatment arms. Pharmacists of the VU University Medical Center, who are independent from the clinical research team, will randomly assign participants by using a computer-generated randomisation list and will prepare the study medication. After the last participant finishes the trial masking will continue until after the data analyses.

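### The primary model could also adjust for baseline FEV1, which is measured anyway: a minor, nearly free improvement, not an error

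*Protocol article*

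**What the plan says.** The primary outcome, exacerbation rate, "will be analysed with generalized linear models for a Poisson distribution" (Statistical analysis, Primary outcome). The same paragraph continues: "Analyses will be adjusted for the variables included in the balancing algorithm for randomisation, i.e. study center, gender, age and current smoking". The wording closes the list at four variables.

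They are the allocation variables. Randomisation and masking describes a "sequential balancing method with study center as the first step in the balancing algorithm, followed by gender, age and current smoking" and gives the reason: "These variables are (potential) prognostic factors and thus should be balanced over the treatment arms". Neither FEV1 nor GOLD stage is in either list.

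Severity nevertheless varies and is measured. Study design and participants states: "The study population consists of COPD patients with GOLD stages II-IV". An entry criterion in Table 1 is "FEV_1_ < 80 % and diagnosis COPD confirmed by a physician". Spirometry measures states: "At t = 0 and t = 12 participants will undergo spirometry", and that section specifies post-bronchodilator values.

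**The concern.** The four variables were chosen because they may predict outcome. Lung function meets that test at least as a possibility in a population that runs from moderate to very severe disease, yet it is neither balanced at allocation nor adjusted for in the analysis. If baseline FEV1 does predict exacerbation rate, part of the random error in the rate ratio is simply the chance difference in FEV1 between the arms. Adjustment removes that part. The time to decide is before unblinding, because adding a covariate after an imbalance has been seen is a data-driven choice.

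**Working it through.** **Inputs from the article.** Rates: the "assumption of 2.45 exacerbations per patient-year in the intervention group and 3.45 in the placebo group"; 94 per group needed; 120 per group recruited, which is 120 × 0.8 = 96 completers after 20% dropout; 1:1 allocation; one year of follow-up.

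**Inputs that must be assumed.** The article gives neither the FEV1–exacerbation association nor the between-patient variation in rate.

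- Log-rate effect per SD of FEV1: b = 0.1, 0.2 or 0.3, that is exp(b) = 1.11, 1.22 or 1.35. Read b as what FEV1 adds beyond centre, gender, age and smoking.
- Between-patient variance of the rate: k = 0.35 or 0.7.

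**The plan's own figure.** For a difference of Poisson means, n = (1.96 + 0.842)² × (2.45 + 3.45)/1² = 46.3, so 47 per group, not 94. Reaching 94 per group would need about 2.03 times the Poisson variance, or k of about 0.34 to 0.35. That discrepancy is a separate matter. It is used here only to choose k = 0.35 as one plausible value.

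**Standard errors at 96 per arm, k = 0.35.**

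- Plain Poisson: √[(1/2.45 + 1/3.45)/96] = √(0.698/96) = 0.085.
- True, with between-patient variation: √[(0.698 + 2 × 0.35)/96] = √(1.398/96) = 0.121.

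**Effect of adding the covariate.** Results come from 1,000 simulated trials per scenario, 96 per arm, gamma-distributed heterogeneity, comparing models with and without one standardised covariate. Power is calculated from the mean robust SE and the design log rate ratio, ln(3.45/2.45) = 0.342.

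| k | b | Robust SE without | Robust SE with | Variance ratio | Power without → with |
|---|---|---|---|---|---|
| 0.35 | 0.1 | 0.1195 | 0.1186 | 0.99 | 82% → 82% |
| 0.35 | 0.2 | 0.1193 | 0.1157 | 0.94 | 82% → 84% |
| 0.35 | 0.3 | 0.1197 | 0.1113 | 0.86 | 82% → 87% |
| 0.7 | 0.1 | 0.1463 | 0.1456 | 0.99 | 65% → 65% |
| 0.7 | 0.2 | 0.1465 | 0.1436 | 0.96 | 65% → 66% |
| 0.7 | 0.3 | 0.1461 | 0.1391 | 0.91 | 65% → 69% |

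The raw rejection fractions, which carry more simulation noise, rose by 0 to 6 points.

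**Check by hand.** The variance removed should be about b² × 2/n. For b = 0.2 and k = 0.35: 0.04 × 2/96 = 0.00083, against 0.1193² = 0.0142, a reduction of 5.9%, which matches the ratio of 0.94.

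**The model as written.** The plain Poisson SE averages 0.0855 to 0.0860 without the covariate and 0.0858 to 0.0862 with it, so it does not fall.

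**Chance imbalance at 120 per arm.** The SD of the between-arm difference is √(2/120) = 0.129 FEV1-SD. A 1.96-SD draw is 0.253 SD. The unadjusted rate ratio then shifts by exp(0.253b) = 1.03, 1.05 or 1.08.

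**The case against.** The strongest case against is that nothing here is wrong. The analysis adjusts for exactly the factors used in allocation, which is standard practice and pre-specified. Randomisation protects the comparison with or without FEV1, and a chance imbalance is part of sampling error, not bias. Every size above rests on assumed inputs, and the gain starts near zero. All of that stands.

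Three stronger readings are tempting, and the article supports none of them.

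- A reader might infer that the article itself establishes FEV1 as a predictor of exacerbations. It does not. The Introduction says that frequent exacerbators lose lung function faster, and the section Vitamin D and COPD relates deficiency to severity. Neither says that baseline FEV1 predicts later exacerbation rate. What remains is that FEV1 is a potential prognostic factor, which is the standard the article sets for its own four.
- A reader might infer that adding FEV1 would narrow the reported interval and so raise the power of the planned test. For the plain Poisson model as written it would not, because that standard error is driven by the event counts and not by variation between patients.
- A reader might want the number of exacerbations in the year before randomisation added as well. The article does not say that this count is recorded.

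The objection does not remove the gain in the estimate itself. Its true variability falls whichever standard error is reported. At k = 0.35 a nominal 95% Poisson interval covers about 83% (1.96 × 0.0853/0.1207 = 1.385). With variance ratios of 0.94 and 0.86 this becomes about 85% and 86%. That helps slightly but does not cure overdispersion.

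**Conclusion.** Minor. This is an optional improvement, not an error or a contradiction. Leaving FEV1 out forgoes an adjustment that costs almost nothing. For assumed rate changes of 11% to 35% per SD of FEV1, the true variance of the log rate ratio would fall by about 1% to 14%, and power under a variance that reflects overdispersion would rise by about 0 to 5 points. The shift from chance imbalance (a factor of 1.03 to 1.08) is the same benefit seen in a single trial, so the two should not be added together. If FEV1 largely overlaps with age, smoking or centre, the gain lies at the low end. The question put to the data does not change: under a log link, and without an interaction with treatment, the adjusted and unadjusted rate ratios target the same quantity.

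**What to change.** In Statistical analysis, Primary outcome, add baseline (t = 0) post-bronchodilator FEV1 % predicted, as a continuous variable, to the pre-specified covariates. Report the model with only the four balancing factors as a sensitivity analysis. Make the change before unblinding.

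The cost is one phrase in the analysis section and one extra model run; the measurement is already planned. For the gain to show in the reported confidence interval, the model must also use a robust or overdispersion-aware variance. Adding the covariate alone will not do that.
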